### Postintervention data collection

All preoperative assessments will be performed at the end of the intervention period. At the end of the protocol and assessments, all volunteers will receive a report with all data evaluations.

### Statistical analysis

A blinded researcher will perform all statistical analyses for this study. The volunteers will be codified by the researcher responsible for randomization to ensure blinding of control and intervention groups. Descriptive statistics including the mean, standard deviation (SD), and quartiles will be applied to summarize the data. The Shapiro Wilk test will be used to investigate data distribution. Data will be expressed as mean, SD, and 95% confidence interval. The primary analysis is to assess the effect of the intervention on 6MWT distance and the secondary analysis is the relationship between 6MWT distance and the lean mass loss.

In this sense, the effect of WBS will be assessed in the context of the following hypotheses:H0: WBS does not improve 6MWT distance and/or does not prevent the loss of muscle mass.H1: WBS increases 6MWT distance and/or prevents the loss of muscle mass.

If the data present a normal distribution, analysis of variance (ANOVA) will be tested for comparisons between the body composition and 6MWT distance change considering three periods of evaluation (preoperative, postoperative, and postintervention). In instances where data are not normally distributed, nonparametric tests will be applied.

The benefits obtained by both groups will be demonstrated through the difference between postintervention results minus PO data with all variables that will be collected. Comparisons between groups will be assessed using the unpaired Student *t* test or Mann-Whitney test, as appropriate.

Effect size will be analyzed using Cohen’s *d*, and the results will be interpreted based on the Cohen classification [34] as follows: small (0.21–0.49), medium (0.50–0.79), or large (> 0.80).

The statistical analysis using correlation will assess the degree of association (or dependence) between improvements in functional tests, body composition data (InBody 720 and DXA), muscular assessment (dynamometry), and concentration of cytokines.

Appropriate correlation tests will be used if normality of distribution, linearity, variability, and homoscedasticity is satisfied from the scatter diagram performed a priori. The correlations will be defined as weak (0.20–0.50), strong (0.50–0.70), and very strong (> 0.70) [35]. The statistical analysis will be performed using SPSS Statistics for Windows, Version 17.0. (SPSS Inc., Chicago, IL, USA) and MedCalc, version 11.4.4.0 (MedCalc Software, Mariakerke, Belgium), adopting a significance level of 5%. Per-protocol and intention-to-treat analyses will be conducted.

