#### Sample size

The sample size calculation was performed using GPower, Version 3.1.3 (Franz Faul Universität Kiel, Germany), based on a previous study by our group performed on BS patients [16] which showed a difference between the distance walked during a 6-min walking test (6MWT) before and after aerobic training of 49.7 ± 15 m. We hypothesize that we will see an improvement in 6MWT distance following WBS to a similar level as our previous study. Therefore, we projected a sample size that would provide 80% power at a significance level of α = 0.05, detecting a variation of 30% as a favorable outcome. These parameters indicate a sample of five volunteers would be required to investigate functional gains after the intervention.

The primary outcome measure for the study will be the 6MWT distance in meters since the distance walked following interventions in patients with chronic conditions is an important tool to assess the efficacy of interventions that theoretically improve functional capacity [16]. Secondary outcomes of this study are to investigate whether the intervention prevents muscle mass loss and whether there is an association between 6MWT distance with lean mass in kilograms [17]. Therefore, since the performance improvement, the prevention of lean mass loss, and the association between these measures represent important outcomes in the present study, the sample size was recalculated. Based on the bivariate normal correlation model, considering a significance level of 5%, a sample power of 95%, and a strong correlation (> 0.70) between lean mass percentage and 6MWT performance as the main outcome, the calculated sample size was 16 volunteers per group. Anticipating a dropout rate of approximately 15%, a total of 36 patients will be included in the present study.

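### H0 and H1 both join 6MWT distance and muscle mass with and/or, so they overlap and conflict with the single named primary outcome

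*Protocol article*

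**What the plan says.** The Statistical analysis section sets out one pair of formal hypotheses. The null is "H0: WBS does not improve 6MWT distance and/or does not prevent the loss of muscle mass". The alternative is "WBS increases 6MWT distance and/or prevents the loss of muscle mass".

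The sentence just before the pair ranks the endpoints differently: "The primary analysis is to assess the effect of the intervention on 6MWT distance". It gives the secondary analysis as the relationship between 6MWT distance and lean mass loss. The Sample size section agrees on the primary ("The primary outcome measure for the study will be the 6MWT distance in meters") and places muscle mass below it: "Secondary outcomes of this study are to investigate whether the intervention prevents muscle mass loss". The same section then bases the final sample size on "a strong correlation (> 0.70) between lean mass percentage and 6MWT performance as the main outcome".

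The between-group comparison is an unpaired t test or Mann-Whitney test on change from the postoperative to the postintervention assessment, planned for all variables. A single 5% significance level is adopted. Sidedness is not stated, although H1 is worded directionally.

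**The concern.** A null and an alternative should divide the possible states of the world between them. Here the same connective appears in both, so the mixed states, where WBS helps one endpoint and not the other, are not assigned to one side. Those states are plausible in early postoperative patients on a restricted diet, where walking distance may recover while lean mass still falls.

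The second problem is the clash with the hierarchy. Two sections make 6MWT distance the only primary. H1 puts muscle mass on an equal footing with it. A null 6MWT result with a favourable muscle mass result is a failed primary under the hierarchy, yet it satisfies H1 as worded. What the trial may conclude in that case would be settled after the data are seen.

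**Working it through.** **1. Do the hypotheses exclude each other?** Let A be that WBS increases 6MWT distance and B that it prevents muscle mass loss. With an inclusive or, H0 is (not A or not B) and H1 is (A or B).

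| True state | H0 | H1 |
|---|---|---|
| A and B | false | true |
| A only | true | true |
| B only | true | true |
| neither | true | false |

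Both hold in the two mixed states. If and is read in both places instead, H0 is neither effect and H1 is both effects, and the mixed states belong to neither hypothesis. Only two pairings are complementary: neither against at least one, and not both against both. The wording selects neither pairing.

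**2. What would each reading do to the error rate?** The 5% is an adopted level, not a derived figure, so there is no calculation of the plan's to reproduce for it.

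- If 6MWT distance alone decides, the primary error is 5%.
- If both endpoints must succeed, there is no inflation, because the rule cannot reject more often than either test alone.
- If either endpoint suffices at an unadjusted 5%, the error rises as computed below.

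Inputs for the third case: 5% per endpoint (Statistical analysis section) and a correlation r between the two test statistics. The article gives no such correlation. The Sample size section assumes more than 0.70 between lean mass percentage and 6MWT performance. Using 0.70 for the change scores is therefore an assumption, and 0 to 0.9 is shown as the range.

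With (Z1, Z2) bivariate normal with correlation r:

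- Two-sided, either direction: 1 − P(|Z1| ≤ 1.96 and |Z2| ≤ 1.96). At r = 0 this is 1 − 0.95² = 0.0975.
- One-sided 5%: 1 − P(Z1 ≤ 1.645 and Z2 ≤ 1.645). At r = 0 this is also 0.0975.
- Two-sided 5%, favourable results only: 1 − P(Z1 ≤ 1.96 and Z2 ≤ 1.96). At r = 0 this is 1 − 0.975² = 0.0494. The single-test reference is 2.5%.

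| r | Two-sided, either direction | One-sided 5% | Two-sided, favourable only |
|---|---|---|---|
| 0 | 9.75% | 9.75% | 4.94% |
| 0.5 | 9.07% | 8.78% | 4.54% |
| 0.70 | 8.35% | 8.04% | 4.17% |
| 0.9 | 7.04% | 6.81% | 3.52% |

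Simulated two-sided t tests with 16 per arm, counting either direction, agree: 9.8%, 8.3% and 7.1% at r = 0, 0.70 and 0.9.

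Relative to the single-test rate, the two-sided figures are 0.0975/0.05 = 1.95 times at r = 0, 0.0835/0.05 = 1.67 times at 0.70 and 0.0704/0.05 = 1.41 times at 0.9.

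**The case against.** The strongest reply is that the article already settles the matter. The sentence before the hypotheses names 6MWT distance as the primary analysis, the Sample size section names it as the primary outcome, and nowhere is muscle mass called co-primary. On that reading the hypotheses are loosely drafted and the primary error is 5%. This stands as far as the error rate goes. It does not rescue the hypotheses, which still overlap and still say something other than the hierarchy.

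A reader might infer that success on either endpoint counts and that the 5% error is therefore nearly doubled. The documents do not support this. No either-endpoint decision rule is stated. Near-doubling in the two-sided calculation requires independent endpoints, whereas the article itself assumes a strong association. The absolute excess over 5% also depends on the unstated sidedness: if only favourable results of two-sided tests count, the rate stays below 5%, although it is still 1.4 to 2 times the 2.5% of one test.

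It may also be said that multiplicity rules for secondary outcomes belong in an analysis plan that is not shown. That is fair, and their absence is not part of this point. The hypotheses, by contrast, are stated in the article, and they are stated wrongly.

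**Conclusion.** Wrong as written. The two hypotheses are not mutually exclusive, and H1 contradicts the single primary outcome and primary analysis named elsewhere in the article. This follows from the text alone and needs no assumption beyond the ordinary inclusive sense of and/or.

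The effect on the error rate is conditional. It arises only if H1 is accepted on either endpoint at an unadjusted 5%. The overall rate is then about 8.4% for two-sided tests at the assumed correlation of 0.70, and the other cases are as tabulated. The figures take the correlation as non-negative and borrow the 0.70 from a related but different quantity.

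**What to change.** Restate H0 and H1 for one quantity: the between-group difference in change in 6MWT distance, postintervention minus postoperative, as already planned. Test it at 5% and state whether the test is one- or two-sided. Give lean mass its own secondary hypothesis, and say that it cannot support the trial's main conclusion by itself, for example by testing it only if the 6MWT result is significant. The planned t test or Mann-Whitney test on change can stay as it is.

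The cost is a few sentences plus a decision on sidedness. The small downside is that a lean mass benefit alone can no longer support the main claim.

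If the investigators want lean mass to be able to carry the trial, the alternative is to declare two primary outcomes and divide the level. Two-sided 2.5% each gives an overall error of 4.94% at correlation 0 and 4.3% at 0.70. At 80% power this needs about ((2.241 + 0.842)/(1.960 + 0.842))² = 1.21 times the sample size per endpoint.

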Conventional gastric bypass surgery, associated with dietary restriction in the postoperative (PO) period, limits physical activity performance and can lead to reductions in skeletal muscle mass and performance [9]. As such, strategies are needed to preserve and ideally enhance functional performance. In this context, whole-body neuromuscular electrical stimulation (WBS), which differs from conventional electrical stimulation, has been recently introduced as a strategy to simultaneously stimulate several large muscle groups. It represents a promising and innovative option to enhance weight loss, improve exercise capacity and peripheral muscle strength, and induce positive systemic effects [10–12]. Several studies have demonstrated that WBS reduces sarcopenia and abdominal fat mass in both young and older sedentary individuals [13]. These studies emphasize the potential effects of WBS—being able to act beneficially when other conventional exercises are contraindicated [13].

Another study showed that WBS could, through an increase in muscle mass, potentiate the action of insulin and thus produce greater uptake of glucose in the muscle as well as reduce the proinflammatory state. These findings may be particularly relevant in the obese population which is predisposed to greater insulin resistance [14].

While WBS may hold promise as a rehabilitation strategy following bariatric surgery (BS), especially in the early stages after surgery, there appears to be no evidence about its applicability in the bariatric PO period.

Therefore, the objective of this study is to evaluate the effects of WBS on body composition, functional capacity, muscle strength and endurance, insulin resistance, and pro- and anti-inflammatory circulating markers in obese patients undergoing BS in the early PO period.

We hypothesize that WBS would enhance functional capacity, muscle strength, and endurance, and reduce inflammation in BS patients when compared with controls (Sham). Moreover, we hypothesized that WBS would reduce fat mass, improve muscle mass, and positively affect insulin resistance and exercise capacity in these patients. We also expect patients to present good acceptance and adherence to the intervention protocol.

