**Fig. 2 Fig2:**
[figure not shown]
Consolidated Standards of Reporting Trials (CONSORT) flow diagram of the study. 6MWT 6-min walking test, CPX symptom-limited or maximum cardiopulmonary exercise testing

The CPX will be performed on a treadmill (Super ATL, Porto Alegre, Rio Grande do Sul, Brazil) using the incremental Bruce protocol. Volunteers will be monitored by a 12-lead electrocardiogram (WinCardio System, Microme, Brasilia, Brazil) supervised by a physician, and encouraged to achieve maximal effort. Heart rate, blood pressure, and subjective responses of dyspnea and fatigue by the CR10 scale [19] will also be measured.

The 6MWT will be performed according to guidelines established by the ATS/American College of Chest Physicians [20]. The object of this test is to walk as far as possible for 6 min over a 30-m corridor. Cardiorespiratory and metabolic variables will be collected breath-by-breath through a portable Oxycon Mobile® ergospirometer (Mijnhardt/Jäger, Würzburg, Germany) throughout the 6MWT.

Blood samples will be collected the morning after a 12-h fast from the upper limb antecubital vein by a qualified professional to quantify fasting glucose levels, insulin, the insulin resistance index by the Homeostasis Model Assessment method (HOMA-IR), and the lipid profile (total cholesterol, high-density lipoprotein cholesterol (HDL-C), low-density lipoprotein cholesterol (LDL-C), very low-density lipoprotein cholesterol (VLDL-C), and triglycerides) [2, 21]. It will also be used to measure the serums concentrations of TNF-α, adiponectin, leptin, and myostatin. These samples will be analyzed by enzyme-linked immunosorbent assay (ELISA) in duplicates using high-sensitivity kits (Quantikine® HS, R&D Systems, Minneapolis, USA) according to the manufacturer’s recommendations [22]. The volunteers will be instructed not to exercise for 48 h preceding the examination and to maintain their usual diet.

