Body composition will be obtained by bioelectrical impedance analysis, performed by an InBody 720 device and dual energy x-ray technique using digital absorptiometry (DXA) [23–26]. The use of both equipment for body composition will ensure all data is collected since the DXA scanning area can be limited and compromise some measures due to the larger abdominal circumference of recruited obese patients. Volunteers will be instructed to undergo a 4-h fast, to wear light clothes, not to have any metal objects in contact with their body, to urinate prior to the examination, not to drink alcohol, and not to perform strenuous exercises the day before the examination [23].

Evaluations of concentric and isometric extension of the dominant knee will be carried out using an isokinetic dynamometer (Biodex Multi-Joint System 3; Biodex Medical System, Inc., Shirley, NY) at least 48 h after the last functional test.

Isometric and isokinetic assessments will be performed using a previously described protocol [27]. The highest absolute concentric extensor and flexor torque as well as a BMI-normalized value, the flexor/extensor ratio, total work, power, and quadriceps femoris muscle fatigue at an angular speed of 60°/s will be measured [27, 28]. Volunteer positioning and the alignment of the mechanical axis, as well as the gravitational correction, will be performed as previously described [27]. Standardized encouragement will be provided by a single evaluator to stimulate volunteers to produce their maximal effort during all tests.

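### About 20 unranked outcomes and an open set of change correlations are tested at 5% with benefit to be demonstrated on every variable; they need an exploratory label, and most have no postoperative value from which to compute the planned change.

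*Protocol article*

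**What the plan says.** All references are to the Protocol article.

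- **Ranking.** Sample size names 6MWT distance as the primary outcome. Its secondary outcomes are prevention of muscle mass loss and the association of 6MWT distance with lean mass. The formal H0 and H1 in Statistical analysis cover only 6MWT and muscle mass.
- **Hypotheses.** The Background goes further: "We hypothesize that WBS would enhance functional capacity, muscle strength, and endurance, and reduce inflammation in BS patients when compared with controls (Sham"), and then "Moreover, we hypothesized that WBS would reduce fat mass, improve muscle mass, and positively affect insulin resistance and exercise capacity in these patients".
- **Scope of testing.** Statistical analysis states: "The benefits obtained by both groups will be demonstrated through the difference between postintervention results minus PO data with all variables that will be collected". It continues: "Comparisons between groups will be assessed using the unpaired Student *t* test or Mann-Whitney test, as appropriate".
- **Level.** The same section ends by "adopting a significance level of 5" per cent, with no distinction between outcomes.
- **Correlations.** The correlation analysis "will assess the degree of association (or dependence) between improvements in functional tests, body composition data (InBody 720 and DXA), muscular assessment (dynamometry), and concentration" (the concentrations meant are the cytokine levels).
- **Further variables.** Evaluations lists a glucose, insulin and lipid panel, says the blood will also be used to "measure the serums concentrations of TNF-α, adiponectin, leptin, and myostatin", and adds knee torque measures for which "the flexor/extensor ratio, total work, power, and quadriceps femoris muscle fatigue at an angular speed of 60°/s will be measured". CPX is also performed, with no endpoint named.
- **Timing.** Postoperative data collection covers only the 6MWT and body composition.

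**The concern.** The article does more than leave multiplicity unmentioned. It sets one significance level for every test, and it uses the language of demonstrated benefit for every variable collected. It also states in advance that WBS should improve strength, inflammation, insulin resistance and exercise capacity relative to Sham, yet no blood, dynamometry or CPX variable is ranked as an outcome.

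With 16 patients planned per arm, suppose the 6MWT comparison is null and one cytokine, lipid fraction or torque index reaches p < 0.05. Read literally, the plan lets that result be reported as a demonstrated benefit that fits a stated hypothesis. Nothing in the article marks it as hypothesis-generating.

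The sentence that licenses these claims also defines change from the postoperative visit, and most of the variables concerned are not measured at that visit.

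**Working it through.** **1. Figure in the plan.** The article states a 5% level per test. It gives no family-wise error rate, so there is none to reproduce.

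**2. Count of unranked variables, from Evaluations.**
- Glucose, insulin, HOMA-IR, total cholesterol, HDL-C, LDL-C, VLDL-C, triglycerides: 8
- TNF-α, adiponectin, leptin, myostatin: 4
- Extensor torque, flexor torque, BMI-normalised torque, flexor/extensor ratio, total work, power, fatigue: about 7
- CPX: at least 1

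8 + 4 + 7 + 1 = 20, before isometric values and fat mass.

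**3. Independent tests, no true effect.** The article does not state sidedness; two-sided 5% is assumed, so each test has a 2.5% chance of a false result favouring WBS.
- Either direction: 1 − 0.95^20 = 64%; expected number 20 × 0.05 = 1.0
- Favouring WBS: 1 − 0.975^20 = 40%; expected number 20 × 0.025 = 0.5

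**4. Correlated tests.** The outcomes are related (HOMA-IR, for example, is an index built on glucose and insulin), so independence gives an upper figure. The document gives no correlations, so a range is assumed. Rates for 20 null outcomes, by simulation:

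| Assumed common correlation | At least one significant, either direction | At least one favouring WBS |
|---|---|---|
| 0 | 64% | 40% |
| 0.3 | 54% | 28% |
| 0.5 | 42% | 21% |
| 0.7 | 30% | 15% |
| 0.8 | 22% | 11% |

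The rows for 0, 0.5 and 0.8 use equicorrelated normal test statistics. The rows for 0.3 and 0.7 use t tests with 16 per arm, which give 43% and 22% at 0.5, in agreement with the table.

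Grouping the variables by domain (3 glucose-insulin, 5 lipid, 4 cytokine, 7 dynamometry, 1 CPX) gives similar figures. With correlation 0.7 within and 0.2 between domains, the rates are 48% and 25%. With 0.5 and 0.1, they are 55% and 30%.

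**5. Correlation analysis.** These tests come on top of the group comparisons. Their number depends on how many functional, body-composition, dynamometry and cytokine variables are entered. The article names no CPX endpoint and does not list the body-composition variables, so no rate can be derived.

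**6. Can the stated change be computed?** Set the sections side by side:
- Evaluations: CPX, 6MWT, blood, bioimpedance and dynamometry are done preoperatively and repeated after the intervention.
- Postoperative data collection: 6MWT and body composition only.
- Statistical analysis: postintervention minus postoperative value, for every variable collected.

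For the 20 variables in step 2 the subtrahend does not exist. The only earlier value is the preoperative one, so their change also contains the effect of surgery in both arms.

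**The case against.** **A hierarchy exists.** A reader might infer that the plan has none, or that the extra tests inflate the error of the main result. The documents do not support either reading. One primary outcome and two secondary outcomes are named, H0 and H1 are confined to 6MWT and muscle mass, and tests on other variables leave the error rate of the 6MWT test unchanged. This part of the objection stands in full.

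**A false WBS effect is not shown to be likely.** In the group comparisons the chance of one favouring WBS is about 11% to 40%. A figure above 50% arises only when both directions are counted and correlation is low. Nor should these rates be read as a multiple of the stated 5%, which is a per-test level. This also stands.

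**The correlations cannot be sized.** A percentage for them would require guessing the variable list. The text speaks of degree of association and grades correlations by strength; it does not say that a significant one establishes a mechanism.

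**The anchor sentence cannot generate these tests as written.** That is correct, but it does not remove them. The variables are remeasured after the intervention, the sentence covers all variables collected, and the correlation analysis names dynamometry and cytokines. It shows a second fault in the same sentence.

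**This belongs in an analysis plan.** Adjustment for lower-ranked outcomes is commonly left there, and silence would be no finding. Here the article itself fixes the level and the claim of demonstrated benefit. Means, confidence intervals and Cohen's *d* are already planned, so the remedy is small.

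**Conclusion.** The point holds as a fault of labelling and wording. About 20 outcomes and an unspecified number of correlations are unranked, are tested at 5%, and fall under a sentence that promises demonstrated benefit. The primary 6MWT inference is not affected.

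For 20 null outcomes, the chance of at least one significant difference favouring WBS is about 21% (11% to 40%), and 42% (22% to 64%) in either direction. These figures rest on two-sided 5% tests, a count of 20 and assumed common correlations of 0.5 (0.8 to 0). The correlation analysis adds an amount that cannot be stated.

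Separately, and without any assumption, the planned change score cannot be computed for blood, CPX and dynamometry variables.

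**What to change.** In Statistical analysis:

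1. Restrict claims of demonstrated benefit to the between-group comparison of 6MWT and, after it, the between-group comparison of lean mass change.
2. Keep the 6MWT-lean mass association as the named secondary association. It is not a treatment claim and need not wait on the two group comparisons.
3. Label all other outcomes (fat mass, CPX, dynamometry, glucose, insulin and HOMA-IR, lipids, cytokines) and all other correlations as exploratory. Report them as estimates with 95% confidence intervals, and say that they are described, not demonstrated.
4. In the same sentence, define change by variable: from the postoperative visit for 6MWT and body composition, and from the preoperative visit for blood, CPX and dynamometry. State that the latter change includes the effect of surgery.

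The cost is wording only, with no new patients or measurements. The downside is that an isolated significant result on a blood marker, a strength index or an unplanned correlation can be reported only as hypothesis-generating.

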### Evaluations (testing procedures or measurements)

All enrolled volunteers will be submitted to anamnesis and the Baecke questionnaire will be administered to collect information about habitual physical activity related to occupation, sports, and leisure activities [18].

After the screening period and signing the informed consent (Additional file 2), the volunteers will return to the laboratory on 4 different days to perform the preoperative evaluations (Fig. 2), which are: 1) maximal CPX; 2) the 6MWT; 3) blood collection; 4) bioimpedance measurements; and 5) isokinetic and isometric peripheral muscle strength and endurance assessments. All evaluations will be performed again following the intervention.

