### Postoperative data collection

In the PO period, the 6MWT and body composition measurements will be performed. These evaluations will occur within 1 week after discharge. Afterwards, volunteers will be randomized to the experimental group or the control group. At the end of the interventional trial, all preoperative evaluations will be performed a second time.

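### Blood markers and HOMA-IR are to be compared as unadjusted absolute changes from a postoperative visit that lists no blood sample; a log-scale model adjusted for the preoperative value is a better choice

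*Protocol article*

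**What the plan says.** All references are to the protocol article.

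- **Statistical analysis** sets one rule for every outcome. Benefit is shown "through the difference between postintervention results minus PO data with all variables that will be collected". The arms are then compared as follows: "Comparisons between groups will be assessed using the unpaired Student *t* test or Mann-Whitney test, as appropriate". The three-period ANOVA in the same section covers only body composition and 6MWT distance, and its fallback is "In instances where data are not normally distributed, nonparametric tests will be applied". No transformation, ratio or baseline adjustment is named.
- **Evaluations** brings fasting glucose, insulin, HOMA-IR and lipids under that rule, and adds of the blood sample: "It will also be used to measure the serums concentrations of TNF-α, adiponectin, leptin, and myostatin".
- **Timing of blood.** Evaluations lists blood collection before surgery and says "All evaluations will be performed again following the intervention". Postintervention data collection agrees. Postoperative data collection lists something narrower: "In the PO period, the 6MWT and body composition measurements will be performed".
- **Standing of these outcomes.** The Background puts insulin resistance and circulating markers in the study objective. Sample size makes 6MWT distance primary, and lean mass and its association with 6MWT distance secondary.

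**The concern.** Two problems meet in one sentence of the plan.

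First, the difference it defines cannot be formed for blood, because no blood value is listed at the PO visit. The natural substitute is the preoperative value, and the change then contains the whole effect of surgery plus six weeks of intervention.

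Second, HOMA-IR is by construction a product of glucose and insulin, and the others are positive concentrations. If a marker halves in everyone, a patient starting at 10 changes by −5 and one starting at 3 by −1.5, although the proportional response is the same. A shift common to both arms cancels in the comparison, but its spread between patients does not. Mann-Whitney ranks the same differences, so it inherits that spread.

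At stake is whether about 16 patients per arm can show anything on outcomes named in the objective. The planned correlations of improvements with cytokines are also touched if absolute changes are used.

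**Working it through.** **The plan's own figure.** The article gives no power or sample size for any blood marker. Its 16 per group comes from a correlation of 0.70 with 95% power at the 5% level. One-sided, the Fisher z formula gives ((1.645 + 1.645)/0.867)² + 3 = 17.4, and simulation gives 94.6% power at n = 16, so the figure reproduces one-sided. A two-sided test needs 20. Here 16 per arm is only an input.

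**Inputs.** From the article: 16 per arm, 1:1 allocation, 5% level (taken as two-sided). Assumed, because the article is silent: log-normal marker, CV 60%, pre/post log correlation ρ of 0.5–0.7, a common 50% fall, and a 30% lower postintervention level with WBS. Baseline is the preoperative value.

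**Model.** s = √ln(1 + 0.6²) = 0.5545. log y = ρ·log x + e + ln 0.5 + arm·ln 0.7, with SD(e) = s√(1 − ρ²).

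**Hand check at ρ = 0.6, baseline median 1.**

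- Baseline mean √1.36 = 1.166, SD 0.6 × 1.166 = 0.700.
- Postintervention means: sham 0.5 × 1.166 = 0.583, WBS 0.35 × 1.166 = 0.408, difference 0.175. SDs 0.350 and 0.245.
- Raw-scale pre/post correlation: (e^(0.6 × 0.3075) − 1)/0.36 = 0.563.
- SD of absolute change: sham √(0.700² + 0.350² − 2 × 0.563 × 0.700 × 0.350) = 0.580; WBS, likewise with 0.245, 0.597.
- SE = √((0.580² + 0.597²)/16) = 0.208. Signal 0.175/0.208 = **0.84** standard errors, t-test power about 13%.
- Ignoring baseline altogether: SE = √((0.350² + 0.245²)/16) = 0.107, signal 1.64. Under these inputs, subtracting the baseline is worse than not using it.
- Log change: SD 0.5545 × √(2 × 0.4) = 0.496, SE 0.496 × √(2/16) = 0.175, signal 0.357/0.175 = **2.03**, power about 50%.
- Log ANCOVA: SD 0.5545 × √(1 − 0.36) = 0.444, SE 0.157, signal **2.27**, power about 59%.

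**Simulated power** (30% effect, ρ 0.5–0.7; "plan" means a Shapiro-Wilk test choosing t or Mann-Whitney on the absolute change):

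| CV | Common fall | Plan | Log-change t | Raw ANCOVA | Log ANCOVA |
|---|---|---|---|---|---|
| 60% | 50% | 16–18% | 41–63% | 43–61% | 51–69% |
| 60% | none | 34–47% | 43–63% | – | 52–69% |
| 40% | 50% | 25–30% | 70–91% | – | 82–94% |
| 80% | 50% | 12–14% | 30–44% | – | 36–49% |

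The plan does slightly better than the hand-calculated 13% because its rule often selects Mann-Whitney. With no WBS effect, rejection was about 5–7% for all methods.

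**Where the gain comes from (first row).** Plan to raw ANCOVA: 43 − 16 = 27 and 61 − 18 = 43 points. Raw to log ANCOVA: 51 − 43 = 8 and 69 − 61 = 8 points.

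**Where it shrinks or reverses.**

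- Rise of 30% instead of a fall (CV 60%, 30% effect): plan 40–60%, log change 43–65%.
- WBS effect of only 10–15% (CV 60%, 50% fall): plan 6–9%, log ANCOVA 9–19%. The effect is missed either way.
- Additive fall and effect (CV 0.3, fall 40%): absolute-change t test 60%, log change 33%, log ANCOVA 44%.

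**Correlations.** At CV 60%, ρ 0.6 and a 50% fall, the absolute changes of two markers correlate 0.00 if their starting levels are independent, 0.19 if those correlate 0.3, and 0.42 if 0.6.

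**The case against.** The strongest reply is that nothing here is invalid. The test holds its level, the arms are randomized, and the primary and secondary outcomes are untouched. Every input behind the power figures is assumed. An analysis plan that is not shown might also name a transformation for skewed assays. All of this is fair except the last as a defence: the article does not leave the matter open but states one rule for all variables.

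A reader might infer more than the documents support:

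- **That surgery produces a large proportional fall which swamps the WBS effect.** The article gives no size, direction, spread or proportionality for any blood marker, and the listed markers need not all move the same way.
- **That the log scale as such brings the gain.** Adjustment on the raw scale already recovers most of it.
- **That the log scale is always safer.** It loses under an additive fall. That model is imperfect for concentrations, since it gave non-positive values in about 1–21% of cases across the settings tried, but it shows that the ordering is not guaranteed.
- **That the planned correlations are bound to be spurious.** This needs starting levels that correlate across markers, which the article does not report.

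One limit is ours: the two schedule figures are not visible. The text alone, including the abstract, places only the 6MWT and body composition at the PO visit.

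**Conclusion.** The point holds in a conditional form. For HOMA-IR and the blood markers, the stated postoperative-based difference cannot be formed from the visits as described, and an unadjusted absolute change from the preoperative value is an inefficient substitute whenever the surgical change scales with a widely spread starting level. Under the main assumptions (16 per arm, CV 60%, ρ 0.5–0.7, 50% common fall, 30% proportional effect) power goes from about 16–18% to 51–69%. Adjustment supplies 27–43 points of that and the log scale about 8 more. The advantage is smaller with no fall, a rise or a small WBS effect, and can turn against the log scale if changes are additive.

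The loss is one of power and interpretability, not of validity. These outcomes are named in the objective but do not drive the sample size or the stated hypotheses, so severity is low to moderate.

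**What to change.** In Statistical analysis:

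1. Reconcile the postoperative-based difference with the visits at which blood is taken, and name the preoperative sample as baseline for blood outcomes if no postoperative sample exists.
2. For HOMA-IR, insulin, triglycerides, TNF-α, leptin, adiponectin and myostatin, regress the log postintervention value on arm, log preoperative value and gender (the stratification factor). Report the WBS/sham ratio of geometric means with its 95% confidence interval. Keep raw medians and quartiles as description.
3. Where these markers enter correlations of change, use log ratios.
4. If a gain in power is cited, state the assumed CV, fall, correlation and effect with it.

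The cost is wording only: no extra visits, samples or patients. Effects are read as ratios rather than differences, and values below the assay limit need a rule fixed in advance. The article says recruitment is under way, so the change should be made before allocation codes are opened.
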